## LIST OF ABBREVIATIONS AND RELEVANT DEFINITIONS

|                      |                                                                                                                           |
|----------------------|---------------------------------------------------------------------------------------------------------------------------|
| APHAB         | Abbreviated Profile of Hearing Aid Benefit questionnaire                                                           |
| AE            | Adverse event                                                                                                      |
| BAHA          | Bone-Anchored Hearing Aid                                                                                          |
| CCMO          | Central Committee on Research Involving Human Subjects                                                             |
| CI            | Cochlear Implant                                                                                                   |
| CVC           | Consonant-vowel-consonant                                                                                          |
| CvZ           | College voor Zorgverzekeraars (Dutch: association of health care insurance companies)                              |
| CROSS         | Contralateral Routing of Sound System                                                                              |
| ENT           | Ear Nose Throat                                                                                                    |
| EQ5D          | Euro-QoL 5D questionnaire                                                                                          |
| GBI           | Glasgow Benefit Inventory                                                                                          |
| HUI(3)        | Health Utilities Index (version 3) questionnaire                                                                   |
| IC            | Informed Consent                                                                                                   |
| METC          | Medical research ethics committee (MREC) (in Dutch: Medisch Ethische Toetsingscommissie (METC))             |
| QALY          | Quality Adjusted Life Year                                                                                         |
| QoL           | Quality-of-Life                                                                                                    |
| RCT           | Randomised Controlled Trial                                                                                        |
| SAE           | Serious adverse event                                                                                              |
| SNR           | Signal-to-noise-ratio                                                                                              |
| SSD           | Single-Sided Deafness                                                                                              |
| SSQ           | Speech, Spatial and Quality of Hearing Scale                                                                       |
| SUSAR         | Suspected Unexpected Serious Adverse Reaction                                                                      |
| THI           | Tinnitus Handicap Inventory                                                                                        |
| TQ            | Tinnitus Questionnaire                                                                                             |
| TTO           | Time Trade Off                                                                                                     |
| VAS           | Visual Analogue Scale                                                                                              |
| UMC (Utrecht) | University Medical Center (Utrecht)                                                                                |
| Wbp           | Personal Data Protection Act (in Dutch: Wet Bescherming Persoonsgegevens)                                   |
| WMO           | Medical Research Involving Human Subjects Act (in Dutch: Wet Medisch-wetenschappelijk Onderzoek met mensen) |

## SUMMARY

**Rationale:** Patients who develop single-sided deafness (SSD) become aware of the importance of hearing with two ears in everyday listening environments. Current clinical practice for patients with SSD consists of optimizing hearing using a Bone-Anchored Hearing Aid (BAHA) or a Contralateral Routing of Sound System (CROSS). With both devices sound awareness on the deaf side can be improved, but they do not provide bilateral auditory input, which is needed to achieve the actual benefits of hearing with two ears. These limitations may be overcome by providing a cochlear implant (CI) and consequently generating auditory input to the affected ear.

**Objective:** The objectives of this study are to evaluate the clinical outcomes gained from having a cochlear implant (CI) over standard health care therapy with either BAHA or CROSS in patients with SSD and to examine the cost utility of cochlear implantation in these patients.

**Study design:** 120 subjects with acute ( $\geq 3$  months and  $\leq 10$  years onset) SSD will be included in this Randomised Controlled Trial (RCT) after their informed consent. 30 Subjects shall receive a CI on the deaf side after randomisation (Group A). The other 90 subjects shall start with a 6-week during test period with either a BAHA on a headband ( $n = 45$ , Group B) or with a CROSS ( $n = 45$ , Group C). After these 6 weeks, patients in group B switch to a test period with a CROSS for 6 weeks and vice versa for patients in group C. After completing both test periods patients in group B and group C will choose for further treatment with a CROSS, a definitive surgically implanted BAHA or no treatment. The follow-up sessions will take place 6, 12, 18, 24, 36, 48 and 60 months after randomisation for participants in all groups.

**Study population:** 120 subjects aged 18 or older with postlingual SSD who are eligible for cochlear implantation.

**Intervention (if applicable):** Cochlear Implantation versus BAHA or CROSS

**Main study parameters/endpoints:** The main outcome will be the performance on the modified Plomp hearing test. Secondary outcome measures will be: performance on the Standard Dutch phoneme test (NvA-list), the Speech intelligibility test with spatially separated sources, the Crescent of sound test (Quentin Summerfield), self-reported benefits in

everyday listening situations and quality of life assessed with the Speech, Spatial and Qualities Hearing Scale (SSQ), Abbreviated Profile of Hearing Aid Benefit (APHAB), Health Utilities Index (HUI3), Glasgow Benefit Inventory (GBI), Hospital Anxiety and Depression Score (HADS), Time Trade-Off (TTO), Visual Analogue Scales (VAS) and EuroQol-5D (EQ5D) and tinnitus questionnaires (Tinnitus Handicap Inventory [THI], Tinnitus Questionnaire [TQ] and Tinnitus Burden Questionnaire). Participants will keep a monthly diary to assess cost utility.

**Nature and extent of the burden and risks associated with participation, benefit and group relatedness:**

The study is considered a non-significant risk evaluation of routine modalities for SSD in clinical practice (BAHA and CROSS) compared to a modality, cochlear implantation, which is already commonly clinically applied in patients with bilateral hearing loss. The evaluation consists of 8 test sessions of 2 hours each, spread out over five years of time, excluding the monthly cost diary. Furthermore, subjects in group B and C will complete three additional questionnaires in their BAHA and CROSS test periods.

# 1. INTRODUCTION AND RATIONALE

## ***1.1 Introduction***

The present study was initiated by [name]. [name] (University Medical Center Utrecht) who approached [name] (Cochlear® Benelux NV) in 2013 for a research collaboration on adult cochlear implantation in patients with single-sided deafness (SSD) with the idea of using a Randomised Controlled Trial (RCT) to compare cochlear implantation to current clinical practice with either a Bone-Anchored Hearing Aid (BAHA) or a Contralateral Routing of Sound System (CROSS).

Patients who develop SSD become aware of the importance of hearing with two ears in everyday listening environments. Current treatment modalities for SSD (i.e. BAHA or CROSS) are effective in restoring sound awareness to the deaf side, but they do not provide benefits with regard to sound localization and improvement in speech perception in noise. These limitations may be overcome by providing a cochlear implant (CI) to the affected ear. The main objective of our study is to evaluate the clinical outcome after cochlear implantation compared to standard health care therapy with either CROSS or BAHA in patients with SSD.

There is no high quality research on the topic of cochlear implantation for patients with single-sided deafness yet. Although current available evidence is limited, the first results of non-randomised trials are promising. In patients with SSD, cochlear implantation leads to an improved quality of life, better speech perception, localization of sounds and reduction of tinnitus complaints compared to BAHA, CROSS or no treatment (Arndt 2010; vd Heyning 2008; Távora-Vieira 2013). Conversely, the significant costs of cochlear implantation over CROSS or BAHA limit the potential use of this modality in patients with SSD. Further high quality research is certainly necessary to provide compelling evidence of sufficiently large benefits of cochlear implantation over CROSS or BAHA in patients with SSD to justify the additional costs. Therefore, our study will be conducted as a RCT to control for biases when assigning subjects to one of three study groups. RCTs are the most rigorous experimental design for establishing the effectiveness of one intervention compared with another (Woolf 1990).

The study is considered a non-significant risk evaluation of routine modalities for SSD in clinical practice (BAHA and CROSS) compared to cochlear implantation, which is already commonly clinically applied in patients with bilateral hearing loss. The risks associated with CROSS, BAHA and cochlear implantation are discussed in Chapter 7.2.

In the rest of the protocol “CROSS”, “BAHA” and “CI” respectively will refer to the technical details and software settings as follows:

- CROSS: (BI)CROSS (clinical practice)
- BAHA: Cochlear® BAHA system 4
- CI: Cochlear® processor system 6 with the *Custom Sound* software

This research will be conducted according to the study details outlined in this protocol and in accordance with Good Clinical Practice (GCP) and finally Dutch legislation.

## **1.2 Rationale**

SSD, or unilateral sensorineural hearing loss, refers to significant or total hearing loss in one ear. Patients who develop SSD become aware of the importance of binaural hearing in everyday listening environments. They experience difficulty in following conversations on their deaf side, in understanding speech in background noise and in determining the localization of sounds (Giolas 1994). Patients with SSD experience a significant disability in auditory function that affected their speech perception, communication and social interaction (Wie 2010).

Normal-hearing listeners gain important benefits from hearing with two ears, also called binaural hearing. One important advantage of binaural hearing is the possibility to determine from which direction sounds are coming (Middlebrooks 1991). The second advantage is the ability to hear sounds and understand speech in noisy environments, especially if sounds come from different directions (Bronkhorst 1988; Dirks 1969; MacKeith 1971). The following three factors contribute to the superior spatial hearing abilities in normal-hearing listeners:

### *1. Binaural squelch*

The brain has a better representation of sounds with auditory input from two cochleas. Normal listeners are able to localize sounds in the horizontal plane (at ear level) with an accuracy of  $\pm 14$  degrees (Stevens 1936). When signals and noise come from different directions, the brain is able to separate them by comparing time, intensity and spectral differences between the two sides. The brain uses interaural differences in intensity and time between the two ears to determine the location of a sound source in the horizontal plane (Akeroyd 2006). The effect is that the brain is able to suppress signals that the listener does not wish to hear (Carhart 1965; Middlebrooks 1991). In normal hearing subjects, the squelch effect provides a gain of 2-4.9 dB in speech reception threshold (Bronkhorst 1988; Carhart 1965; MacKeith 1971).

## 2. Binaural summation

When identical signals are presented bilaterally, there is an advantage when hearing with both ears instead of just one alone. The brain uses binaural redundancy and binaural loudness summation to produce this advantage. Signal threshold is improved by 2–6 dB in the binaural listening condition over the monaural listening condition (Kamal 2012).

## 3. Head shadow effect

When listening to speech in noise, the head acts as an acoustic barrier that attenuates noise on the side contralateral to the signal. Therefore, when one ear is closer to the noise source, adding a second ear contralateral to the noise provides an ear with a better signal-to-noise ratio (SNR). The head shadow effect is purely geometric and does not require binaural processing by the brain. The head shadow effect is more pronounced at high frequencies, towards as much as 10-16 dB in frequencies above 1 kHz (Shaw 1974, Festen 1986).

During the last decades, cochlear implantation has become a widely accepted intervention in the treatment of patients with severe to profound bilateral sensorineural hearing loss. Cochlear implants (CIs) replace the function of a deaf human cochlea. A microphone, mounted to the skull of a patient, receives the sound waves. This microphone is connected to an electrode, which will be surgically implanted in the cochlea. The electrode replaces the function of the hair cells in the cochlea, generating frequency specific pulses resulting in signals from the auditory nerve to the auditory cortex.

Currently, it is standard clinical practice to provide a CI unilaterally in patients with bilateral profound to severe hearing loss. However, based upon the previous described well known advantages normal-hearing listeners derive from hearing with two ears, bilateral cochlear implantation is growing in popularity (Van Schoonhoven 2013). Although many patients with a unilateral CI achieve high levels of spoken word recognition when speech is presented in quiet, even the most successful users still experience difficulty in the presence of competing sounds and are poor at identifying the localization of sounds.

A recently published review showed a significant benefit of bilateral implantation in localization and speech perception in noise over unilateral cochlear implantation (Van Schoonhoven 2013). However, they highlighted the lack of high quality studies concerning the effectiveness of bilateral implantation, preferably RCTs. At this moment our study group is working on a RCT in which one group receives both CIs simultaneously and the other group receives the second implant after a 2-year delay. The results concerning the benefit of bilateral versus unilateral cochlear implantation will be presented later this year.

Up to now, patients with SSD are not considered candidates for cochlear implantation. In the Netherlands, current clinical practice for SSD consists of treatment with a CROSS, BAHA or no treatment. In CROSS, sound is routed from a satellite microphone on the deaf side into the hearing ear (Baguley 2006). If patients are not satisfied with CROSS therapy, placing of a BAHA is the next modality. A BAHA is a percutaneous titanium screw in the temporal bone of the skull, enabling direct transduction of vibrations to the contralateral cochlea (Hol 2004). Before a BAHA is implanted surgically, patients undergo a test period with a BAHA on a headband, simulating the effect, but avoiding the operation.

In 2006, Baguley et al. performed a meta-analysis and concluded that there are only four studies, with several methodological short-comings (i.e. study design, order effect, selection bias, underpowered studies), that compare CROSS to BAHA for patients with SSD. They did not find a significant improvement in auditory localization with either CROSS or BAHA (Baguley 2006). Speech discrimination in noise and subjective questionnaire measures of auditory abilities found BAHA favourable to CROSS and CROSS favourable to the unaided condition. In a more recent review, Bishop et al. stated that the shortcomings in the studies of this meta-analysis have not been overcome since (Bishop 2010). They concluded that the two approaches, both BAHA and CROSS, seemed to be effective in addressing the head shadow effect and restoring sound awareness to the affected side, but minimal to no benefits were found with regard to sound localization and improvement in speech perception.

The perceptive effects of binaural hearing can only be achieved with bilateral auditory input, which cannot be provided with either BAHA or CROSS. In both situations the contralateral cochlea is used to perceive sounds from the deaf ear instead of actual stimulation of the affected cochlea. Therefore patients with SSD still experience difficulties with binaural hearing. Approximately 55% of patients with SSD are not satisfied with current treatment modalities and prefer natural adaptation rather than implanting a BAHA (Desmet 2012). In 45% of these cases the inadequate speech understanding in noise is the main reason for rejection.

As quoted earlier in this paragraph, CIs restore the function of a deaf human cochlea; this way the old situation of binaural hearing may be recovered. Until now, only few non-randomised studies have been conducted on the topic of SSD and cochlear implantation. In unilaterally deaf patients ipsilateral cochlear implantation leads to significantly reduced error rates in spatial hearing tests with speakers located at different angles around patients compared to CROSS or BAHA error rates (Arndt 2010). Furthermore, the authors tested

several conditions for speech comprehension. With noise coming from the normal hearing side and the sound coming from the deaf side, speech comprehension is improved in the cochlear implant situation compared to BAHA, CROSS and the unaided situations 6 months after implantation (Arndt 2010).

Next to these audiological benefits, CIs entail other possible benefits for patients with SSD. Several studies found that cochlear implantation helps to reduce tinnitus (Arndt 2010; vd Heyning 2008, Távora-Vieira 2013). The paradigm is that tinnitus results from peripheral deafferentation leading to a low stimulus state in the cortex. Once the afferent stimuli are back, which can be achieved with cochlear implantation, the tinnitus resolves (vd Heyning 2008).

Furthermore, both the audiological benefits and the absence of tinnitus result in a better quality of life (QoL) for patients with single-sided deafness. Távora-Vieira and colleagues assessed the QoL in their population with SSD patients using the Speech, Spatial and Qualities of Hearing Scale, consisting of subsections assessing speech understanding, spatial hearing and quality of hearing (Távora-Vieira 2013). They found a significant improvement on all three subscales for their study population three months after implantation. Arndt et al. showed significant improvement on both the Speech and Spatial sections of the SSQ after cochlear implantation (Arndt 2010).

While waiting for the results of ongoing RCTs evaluating the effectiveness of bilateral cochlear implantation in patients with severe to profound bilateral deafness, based on current knowledge bilateral cochlear implantation seems to be preferable compared to unilateral implantation when localization of sound and speech perception in noise are concerned (Van Schoonhoven 2013). The benefits of the natural binaural situation of hearing with two ears can only be achieved if both ears receive auditory input. For unilateral deaf patients, current treatment modalities with either CROS or BAHA do not deliver bilateral auditory signals and therefore patients with SSD experience difficulties with binaural hearing. For this reason, further prospective high quality research evaluating the treatment modalities for patients with SSD should be conducted.

## **2. OBJECTIVES**

The main objective of our study is to evaluate the clinical outcome after cochlear implantation over standard health care therapy with either CROSS or BAHA in patients with SSD. As a

final point of interest, this study will also examine the cost utility of cochlear implantation for patients with single sided deafness.

### 3. STUDY DESIGN

The study design is illustrated in Figure 1 (next page). Patients participate after Informed Consent is obtained. In the dark blue squares of the figure, the different subsequent steps after inclusion are noted. The different time-points for follow-up are outlined in the yellow squares.

When subjects are selected, the following characteristics will be documented in a Case Report Form: gender, age, highest level of education, duration of unilateral deafness, anatomical and aetiological issues as well as psychological and motivational attributes.

After inclusion, subjects will be randomly allocated (see section 6.2 Randomisation, blinding and treatment allocation) to one of three treatment groups:

1. Group A: cochlear implantation
2. Group B: 6-week during test periods with first BAHA, then CROSS
3. Group C: 6-week during test periods with first CROSS, then BAHA

Subjects in group A, the cochlear implantation group, will receive a CI directly after randomisation. The device will be programmed 3-7 weeks after surgery, which is standard CI care.

Subjects in group B shall start with a 6 weeks during test period with a BAHA on a headband. After the 6 weeks, these subjects switch to another test period of 6 weeks with a CROSS. In group C, subjects start with a CROSS and after their first 6-week test period they switch to a test period with a BAHA on headband for 6 weeks. After these two test periods, three questionnaires will be filled out (SSQ, APHAB and GBI; see Section 6.1.2. Secondary study parameters/endpoints). The participants in groups B and C complete both test periods after 12 weeks. The reason for this cross-over is to control for bias caused by the order effect, which means that participants will judge the second modality influenced by their experience using the first modality. Since we have created two groups with the opposite sequence, the order effect is eliminated. After completing both test periods, subjects will be seen in our clinic and have to choose for further treatment with either CROSS, a definitive surgically implanted BAHA or no treatment (if they found none of the modalities helpful).

Figure 1: study design

[figure not shown]

Legend: SSD: single-sided deafness, N: number of subjects, CI: cochlear implant; BAHA\*: bone-anchored hearing aid on headband, BAHA (def): definitive surgically implanted BAHA, CROSS: contralateral routing of sound system, FU: follow-up.

In all groups the objective and subjective follow-up measurements shall take place at the same time-points. All questionnaires outlined in section 6.1.2. will be filled out.

During the first two years, subjects will be evaluated at 6, 12, 18 and 24 months after randomisation. During this period, the cost utility diary will be filled out every month. Afterwards, we will continue with follow-up on yearly basis for 3 more years (i.e. 36, 48 and 60 months post-randomisation). The cost utility diary will then be filled out every 3 months, to minimize subject burden.

A sample size of 30 subjects in group A and 45 subjects in group B and C each is designed to allow valid statistical assessment of cochlear implant benefit (see Section 4.4 Sample size calculation).

Patients with an onset of unilateral hearing loss between  $\geq 3$  months and  $\leq 10$  years before time of inclusion are eligible for inclusion (see also Section 4.2 Inclusion criteria). The reason for the three month interval after onset of deafness is that clinical practice nowadays is to first treat without hearing aids (for instance for sudden deafness with corticosteroids) and to await the natural course of the deafness. When the patient remains unilaterally deaf, he/she is eligible for inclusion in the study. When patients became deaf before this study was started, they are eligible for this study when the duration of deafness is  $\leq 10$  years. During this interval, adaptation to the monaural situation occurs and becomes irreversible thereafter. That is the reason why this cut-off point is established.

Subjects shall be randomised into one of the three groups using a strict randomisation process (see Section 6.2 Randomisation, blinding and treatment allocation). Subjects willing to participate must be informed that they can be assigned to either modality and accept to submit to this randomisation. It is only after the subject has signed their consent form that he/she is informed of the assigned group.

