### 6.2 Randomisation, blinding and treatment allocation

120 subjects will randomly be assigned to one of the three study groups: 30 in the CI group, 45 in the first-BAHA group and 45 in the first-CROSS group. A website randomisation

program, developed by the Julius Center, UMC Utrecht (<http://www.juliuscentrum.nl/random/>) shall be used to divide the subjects into the groups.

The randomisation chart is established before the start of the study by an independent data manager. When a local executor recruits a subject, the physician can log on to the site and enter the subject's characteristics. A block randomisation model will be used to make sure that the ratio CI:CROSS:BAHA subjects will be about equal ( $30:45:45 = 2:3:3$  per block). The physician will receive an allocation group number on his/her screen within a few seconds. It is only after the subject has signed the Informed Consent form that he/she is randomised and informed of the assigned group.

Logically, blinding is not possible since both patients and doctors will be able to see from the outside whether subjects have received a CI, BAHA or CROSS.

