## **8. STATISTICAL ANALYSIS**

The aim of the study is to evaluate the clinical outcome after cochlear implantation, compared to BAHA, CROSS or unaided conditions, measured as speech perception in noise, sound localization, tinnitus and quality of life in patients with SSD. Also, a cost utility analysis will be performed (see section 6.3.2).

Overall, the study is an RCT, but subjects in group B and C run through the same two test periods within the first 3 months, afterwards they shall be treated with their modality of choice. As discussed previously, we expect 55% of patients in group B and C to choose for no treatment, we randomise more subjects in these groups (Desmet 2012). Thus equal comparison with the CI group will be possible during follow-up.

Major test intervals are the same in all study groups, namely 6, 12, 18, and 24 months after randomisation. After the first two years, subjects will be evaluated on yearly basis for three more years (36, 48 and 60 months).

The primary outcome will be the performance on the modified Plomp hearing test. The data are quantitative and will be presented as continuous variables. Between-group mean differences, rate differences and rate ratios with 96% confidence intervals will be calculated. Differences between the three groups will be analysed using the Kruskal Wallis test.

The secondary outcomes will be the performances on the other auditory tests and the questionnaires (see Section 6.3). Analyses of between-group differences will be performed with Chi-square-tests for categorical outcomes and Kruskal Wallis tests for continuous outcomes. Within-subject comparisons will entail differences of mean values. These will be analysed using paired t-tests for continuous measures.

Missing values will be imputed using multiple imputation and all analyses will be performed on an intention-to-treat basis.

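### Opposite BAHA/CROSS sequences balance the order effect but do not eliminate it, and the only within-subject test named in the protocol ignores the randomised sequence

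*Protocol*

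**What the plan says.** Protocol Section 3 randomises Groups B and C to the two device orders, and Section 6.2 gives the numbers: "45 in the first-BAHA group and 45 in the first-CROSS group". Section 3 gives the reason for the cross-over as control of the order effect, described as the risk that "participants will judge the second modality influenced by their experience using the first modality". It then concludes: "Since we have created two groups with the opposite sequence, the order effect is eliminated".

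Each test period lasts 6 weeks, and "The participants in groups B and C complete both test periods after 12 weeks". Since 6 + 6 = 12, there is no wash-out. The outcomes collected are three secondary questionnaires: "After these two test periods, three questionnaires will be filled out (SSQ, APHAB and GBI"). The Summary instead places these questionnaires in the BAHA and CROSS test periods, and Section 5.1 has these patients evaluated after 6 and 12 weeks.

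Section 8, in its paragraph on secondary outcomes, says: "Within-subject comparisons will entail differences of mean values", and then: "These will be analysed using paired t-tests for continuous measures". It mentions no period, sequence or carry-over term. It also states: "Missing values will be imputed using multiple imputation and all analyses will be performed on an intention-to-treat basis".

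**The concern.** In a two-period, two-sequence cross-over, running both orders spreads a period effect evenly over the devices. The effect is still in the data: it moves the BAHA-minus-CROSS difference in opposite directions in the two groups. An analysis that pools all the differences and disregards the group counts that movement as random variation. The randomised sequence is what allows it to be separated out.

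The order effect as Section 3 describes it, with the first device colouring the judgement of the second, is also a form of carry-over. If it is equally strong in both orders it behaves like a period effect and cancels from the mean. If it depends on which device came first it does not cancel, and neither the opposite sequences nor a wash-out protects against it here.

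At stake are the precision of the BAHA versus CROSS comparison and an accurate account of what the design can control. Section 1.2 of the protocol itself lists the order effect among the shortcomings of earlier studies comparing these devices.

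**Working it through.** **Plan's own figure.** The protocol gives no sample size or power for the BAHA/CROSS contrast. The 27 per group in Section 4.4 concerns the modified Plomp test between parallel groups. It reproduces (5 dB difference, SD 5 dB, two-sided alpha 0.05, power 95%: exact t calculation 26.99; 27/0.9 = 30), but has no bearing on this point.

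**Inputs.** From the protocol: 45 patients per sequence, two adjoining 6-week periods, and the paired t-test as the only within-subject method named. Assumed, because the protocol gives neither: a period effect π (second period minus first) of 0.25 to 1.0, and a device difference τ of 0.3. Both are in units of the within-sequence SD of the within-patient difference. Also assumed: each questionnaire is completed once per device, without which there is no within-patient contrast.

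**Model.** Let d = BAHA − CROSS, with SD 1 within each sequence.
- Group B (BAHA first): mean of d = τ − π
- Group C (CROSS first): mean of d = τ + π

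**Precision at 45:45.** The pooled mean of d is τ, so there is no bias. The pooled variance is about 1 + π². The paired-t standard error is therefore √(1 + π²) times the period-adjusted one, and the effective number of patients is 90/(1 + π²).

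| π | SE ratio | Effective N of 90 | Power at τ = 0.3, paired t | Power, period-adjusted | Type I error, paired t |
|---|---|---|---|---|---|
| 0.25 | 1.03 | 85 | about 79% | about 80% | about 4.4% |
| 0.5 | 1.12 | 72 | 73% | about 80% | about 3% |
| 1.0 | 1.41 | 45 | 51% | about 80% | about 0.6% |

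Power and type I error are simulated. Type I error below 5% means that the paired test is conservative.

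**Bias with unequal completion.** Bias of the pooled mean = π(nC − nB)/(nB + nC). With π = 0.5:
- 42:45 gives 0.5 × 3/87 = 0.017 SD
- 35:45 gives 0.5 × 10/80 = 0.06 SD
- 30:45 gives 0.5 × 15/75 = 0.10 SD

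At 35:45 the simulated type I error of the paired test is still about 5% for π from 0.25 to 1.0, because the inflated variance offsets the shift. It reaches about 9% at 30:45 with π = 0.5. The period-adjusted estimate is unbiased, with about 5% type I error, in each of these cases.

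**Carry-over.** A carry-over of 0.3 SD in one sequence only shifts both the paired and the period-adjusted estimates by 0.3/2 = 0.15 SD, with type I error of 28% to 29% for either. An equal carry-over in both sequences leaves both estimates unbiased at 45:45.

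**The case against.** The best defence is that Section 8 never says the paired t-test is for the test periods. Its sentence fits change from baseline to follow-up just as well, and details of the cross-over analysis may sit in a statistical analysis plan that is not shown. This stands in part: the link is an inference from the paired t-test being the only within-subject method stated, and the precision loss applies only if it is used that way. It does not rescue the Section 3 sentence, which is wrong whatever the analysis.

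A reader might infer that unequal drop-out biases the device comparison as planned. The protocol does not support that. It plans 45:45 and gives no sign that one order would lose more patients. Bias also requires a period effect, and 42:45, a loss in one sequence of the 3 subjects that Section 6.5 allows for, gives only 0.017 SD at π = 0.5. Multiple imputation under intention to treat could restore the balance, although the protocol does not say whether sequence enters the imputation model, and imputation would not recover the lost precision.

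A reader might also infer that counterbalancing does nothing against carry-over. That is too strong: carry-over of equal size cancels from the mean, and Section 3 does not say that the influence differs by device. Nor would period adjustment cure carry-over that does differ.

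Finally, BAHA versus CROSS is not a stated objective and carries no power claim. That limits the weight of the point. It does not remove it, because Section 3 offers control of order bias as the reason for the cross-over.

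**Conclusion.** The point holds in a limited form. Section 3 overstates what opposite sequences achieve: they balance an additive period effect and equal carry-over, and leave differential carry-over uncontrolled. If the paired t-test is used for the BAHA-minus-CROSS contrast, the cost is mainly precision: a standard error 3% to 41% wider over the assumed range of π, negligible at the low end and material only for period effects of about 0.5 SD or more. There is no bias from an additive period effect at 45:45 and no excess of false positives. The sizes rest on assumed values of π and τ, on an additive period effect, and on each questionnaire being completed for each device. Three secondary questionnaires are affected. The change is worth making because it costs almost nothing and is valid whether or not a period effect exists.

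**What to change.** In Section 8, or in the analysis plan, specify a period-adjusted cross-over analysis for SSQ, APHAB and GBI from the test periods. Either of these serves:
- Compare the within-patient differences, taken as first period minus second period, between Groups B and C with a two-sample test. Half the difference in means estimates the device effect.
- Fit a mixed model with fixed device, period and sequence and a random subject.

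Report the device difference with its confidence interval, the period effect, and results by sequence. Include sequence in the imputation model.

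In Section 3, replace the claim of elimination with wording such as: *the order effect is balanced across sequences and adjusted for in the analysis; differential carry-over cannot be excluded*. State whether the questionnaires are completed after each period or only after both. If after each, add a first-period-only comparison of Group B with Group C as a sensitivity analysis for carry-over; it is between patients and so less precise.

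The cost is a few sentences and one degree of freedom. No extra patients or visits are needed. Extra data would be needed only if the questionnaires are not already completed for each device.
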